### Objectives

The MS-CEBA study aims to identify possible different CEBA profiles and the relationships between such CEBA profiles and societal participation in PwMS. If different CEBA profiles can be established, the aim is to validate the CEBA profiles found in a new group of PwMS. If successful, our aim is to develop a compact neuropsychological screening instrument that is feasible for use in clinical practice and which allows the timely identification of specific CEBA profiles without putting an unnecessary load on PwMS. With this compact screening instrument, PwMS can be timely referred to the neuropsychological rehabilitation treatment most suitable for their specific CEBA profile. Subsequently, by means of a qualitative evaluation, it will be assessed whether this method of selecting treatment indeed proves effective and the selected treatment is suitable for the given CEBA profile or whether, in future research, the existing neuropsychological treatments should be adapted or combined to meet the needs of PwMS. All of this is done with the overarching aim to improve societal participation and quality of life of PwMS. These objectives and the associated subobjectives are presented in Table 1. The study will be divided into 3 phases, pertaining to [1] identification of the CEBA profiles, [2] validation of the profiles and development of the screening instrument, and [3] evaluation of the recommended neuropsychological rehabilitation treatment.

**Table 1 Tab1:** Objectives of the MS-CEBA study

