### Data collection

#### Primary outcome

The primary outcome of the MS-CEBA study are the CEBA profiles, which are latent and thus need to be derived from the scores on neuropsychological tests and questionnaires used to assess the CEBA domains. Through the use of a latent profile analysis, as described in the *Statistical Analysis* section, CEBA profiles will be revealed based on the raw scores of the tests and questionnaires used.

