### Statistical analysis

For analysing the data, Statistical Package for the Social Sciences (SPSS) version 28.0 and/or R, possibly combined with Latent GOLD version 6.0 [50], depending on the availability of suitable packages in R, will be used. For all analyses, the nominal significance level will be set at α = 0.05, 2 sided. The numbering of the analyses described below corresponds to the numbering of the objectives displayed in Table 1*.* In the following, T0 refers to the first group of 300 PwMS, and T1 refers to the retesting of 54 PwMS.

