**Phase 1: Identification of possible CEBA profiles.** 1a) Summary statistics will be computed, describing percentages of PwMS (n = 300) with CEBA symptoms, based on scores on the neuropsychological tests and questionnaires regarding each CEBA domain; 1b) MANOVAs with follow-up ANOVAs will be computed comparing PwMS *(n* = 300) to HCs (*n* = 100) on scores on the neuropsychological tests and questionnaires regarding the Cognitive and Behavioural domain, and ANOVAs will be computed comparing PwMS to HCs on scores on questionnaires regarding the Energetic and Affective domain; for 1c) and 1e) a three-step mixture analysis will be computed [51]: step 1 is a latent profile analysis to identify clusters of PwMS with common CEBA profiles; step 2 is to estimate the posterior cluster membership probabilities of the model from step 1 for each PwMS in the sample, and step 3 is to relate the cluster membership probabilities from step 2 to relevant predictors, i.e., a regression analysis will be carried out to estimate the relationship between the CEBA profiles and the demographic and disease-related variables, with an adaptation to account for the fact that cluster membership is estimated, rather than observed; for 1d) repeated measures MANOVAs will be computed comparing T1 (n = 54) to T0 (n = 300) on the scores on neuropsychological tests and questionnaires for the Cognitive and Behavioural domain separately; if a time effect is indicated, these will be followed by post hoc analyses (repeated measures ANOVAs), to assess which variable(s) the time effect pertains to. A repeated measures ANOVA will be computed comparing T1 to T0 on the scores on questionnaires regarding the Energetic and Affective domain separately; 1f) regression analysis will be carried out, considering two competing models: model 1, using the membership of the CEBA profiles as a predictor; and model 2, using the most distinguishing outcome variables (scores on neuropsychological tests and questionnaires in each of the CEBA domains) as predictors.

**Phase 2: Validation of CEBA profiles and development of the CEBA screening instrument.** 2a) The posterior cluster membership probabilities of the selected latent profile model from Phase 1 will be estimated for each of the PwMS in the new sample (n = 100). The equality of the distributions of membership probabilities of the new sample and Phase 1 sample will be tested using a chi-square test. 

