### Sample size

The sample size calculations provided below were performed following *G*Power* [52]. Since for objective 2b and objectives 3a and 3b (Table 1), no statistical analyses will be carried out, a sample size calculation is not relevant for these objectives.

With regard to objectives 1a and 1c, here, the main study parameter is the CEBA profile, which is latent and thus needs to be derived from performance on neuropsychological tests and questionnaires regarding the CEBA domains. For identification of the CEBA profiles, latent profile analysis will be performed. A minimum sample size of 300 is suggested for latent profile analysis to ensure that there is sufficient power to estimate all model parameters and recover the true number of classes [53, 54]. Therefore, the aim is to include a minimum of 300 patients. For objective 1b, the main study parameters are possible differences between PwMS and HCs on neuropsychological tests and questionnaires regarding symptoms in the different CEBA domains, which will be investigated through the performance of MANOVAs and ANOVAs. A power calculation (with a medium effect size [Cohen’s f] = 0.5, α = 0.05, power = 0.95) results in a minimal sample size of n = 60, which is expected to be exceeded with our goal of including 300 PwMS and 100 HCs for comparison of performance in the CEBA domains. With regard to objective 1d, here, the main study parameters are possible differences in CEBA symptoms between T0 and T1, which are derived from scores on neuropsychological tests and questionnaires regarding the CEBA domains. To investigate the extent to which individual CEBA symptoms are stable over time, repeated measures MANOVAs and ANOVAs will be performed to compare T0 to T1. Within-between interactions will be used. Here, a power calculation using repeated measure analysis (with medium effect size Cohen’s f = 0.5, α = 0.05, and power = 0.95) results in a total sample size of n = 54. Therefore, the aim is to include a minimum of 54 patients for comparing T0 to T1. Since objectives 1e and 1f, as well as objective 2a, depend on the CEBA profiles yet to be identified, the corresponding analyses are considered exploratory, and therefore, no sample size calculation will be provided at this stage. At a later stage, after the CEBA profiles have been identified, sample size calculations for these objectives will be provided, again using *G*Power* [52].

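### Profiles fitted to raw scores may partly reflect skewness if the within-class model is normal: clarify what raw means and add a comparison fit

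*Protocol article*

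**What the plan says.** Under *Primary outcome* the protocol article states: "The primary outcome of the MS-CEBA study are the CEBA profiles, which are latent and thus need to be derived from the scores". It then fixes the scale of the input, with the profiles to be found "based on the raw scores of the tests and questionnaires used".

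Under *Statistical analysis*, 1c and 1e, it describes a three-step mixture analysis in which "step 1 is a latent profile analysis to identify clusters of PwMS with common CEBA profiles". Neither section mentions a within-class distribution, a transformation or a check for skewness. Software is left open: SPSS and/or R, "possibly combined with Latent GOLD version 6.0 [50], depending on the availability of suitable packages in R".

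Whether profiles exist is itself a research question. *Objectives* makes the next phase conditional: "If different CEBA profiles can be established, the aim is to validate the CEBA profiles found in a new group of PwMS". The Phase 2 check (2a) applies the Phase 1 model to 100 new patients, after which "The equality of the distributions of membership probabilities of the new sample and Phase 1 sample will be tested using a chi-square test".

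**The concern.** A latent profile analysis in its usual form assumes that each score is normally distributed within a class. A right-skewed score breaks that assumption even when there is only one class. The mixture can repair the misfit by adding a class for the tail, such as a small slow or high-symptom group, although nobody belongs to a separate population. This needs no correlation between scores, so it is a different mechanism from local dependence or confounding by age.

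Skewness is plausible for timed tests and for symptom questionnaires with many low values. Table 2 includes a trail-making test and scales for mood, fatigue and dysexecutive behaviour. The article gives neither scoring nor distributions, however, so this remains an assumption.

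If it holds, part of the primary outcome could describe the shape of a few scores and not combinations of symptoms. The same profiles feed the regressions in 1e and 1f, the screening instrument and its treatment advice.

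**Working it through.** **The plan's own figure.** *Sample size* says "A minimum sample size of 300 is suggested for latent profile analysis". It gives no number of classes, separation or number of indicators, so 300 cannot be reproduced by formula. It is taken here as given.

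**Inputs from the article.** n = 300 in Phase 1, n = 100 in Phase 2, raw scores, latent profile analysis. Table 2 assigns eleven instruments to a CEBA domain: three participant questionnaires (leaving out the participation scale), two proxy questionnaires and six tests. Eleven scores therefore corresponds to one score per instrument. The article does not say how many scores enter the model.

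**Assumptions.** One homogeneous population; mutually independent scores; normal within-class model; class count chosen by lowest BIC; the degree and shape of skewness.

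**What BIC requires.** With K classes and p = 11 scores, the parameter count is (K − 1) + Kp + p for common variances and (K − 1) + 2Kp for free variances.
- One class: 22 parameters.
- Two classes: 1 + 22 + 11 = 34 (common) or 1 + 44 = 45 (free).
- Extra penalty for the second class: 12 × ln 300 = 12 × 5.704 = 68.4 (common) or 23 × 5.704 = 131.2 (free).

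A second class is preferred to one once twice the log-likelihood gain exceeds that figure. Skewness alone can supply the gain.

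**Skewness of a lognormal score** with log-SD s is (e^{s²} + 2)·√(e^{s²} − 1):
- s = 0.3: 3.094 × 0.307 = 0.95
- s = 0.4: 3.174 × 0.417 = 1.32
- s = 0.5: 3.284 × 0.533 = 1.75

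**Main simulation** (60 runs per setting, K = 1 to 4). Share of runs selecting two or more classes when the true number is one:

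| Skewed scores (of 11) | Skewness | Common variances | Free variances |
|---|---|---|---|
| none | 0 | 0% | 0% |
| 2 | 0.95 | 3% | 0% |
| 2 | 1.32 | 32% | 15% |
| 2 | 1.75 | 82% | 77% |
| 4 | 0.95 | 13% | 5% |
| 4 | 1.32 | 68% | 75% |
| 4 | 1.75 | 98% | 100% |

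After log transformation (tested at skewness 1.32) the share was 0%. The standard error near 50% is √(0.5 × 0.5 / 60) = 6.5 percentage points. An observed 0 of 60 is compatible with up to about 3/60 = 5%.

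**Repeats.** A smaller repeat (30 runs, K = 1 to 3) gave, as common / free:
- two scores: 7/0, 37/17 and 87/77%
- four scores: 7/10, 70/90 and 100/100%

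The 90% is the only value clearly above the main range. A further repeat with common variances gave 10, 53 and 83% for two scores and 7, 70 and 97% for four.

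**Another shape.** With 10 independent gamma scores (common / free variances):
- all ten skewed: 0/0% at skewness 0.5, 52/100% at 1, 100/100% at 1.5
- two skewed at 1.5: 97/93%
- all ten at skewness 2 after rank-based normalising: 0/0%

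Tail shape therefore matters as well as skewness.

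**Phase 2 check.** A spurious three-class solution (ten gamma scores, skewness 1.5, n = 300) was applied to 100 new patients from the same homogeneous population. The chi-square test rejected equality in 5 of 150 replicates, or 3%. About 97% of spurious solutions would have passed.

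**Cost of transforming.** Simulations contained a genuine minority affected on only two of 11 scores (40 runs, common variances, K = 1 or 2):

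| Group size, shift | Found on raw scores | Found on normal scores |
|---|---|---|
| 10%, 3 SD | 100% | 43% |
| 10%, 2.5 SD | 98% | 15% |
| 7%, 3 SD | 100% | 0% |

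A repeat gave 97–100% on raw scores and 3–40% on normal scores. With three or four affected scores the group was still found in 95–100% of runs.

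**The case against.** The strongest objection is that *raw* is over-read. The section that follows *Primary outcome* mentions normative data, so raw may simply mean not adjusted to norms. That would not exclude a log scale or a non-normal within-class distribution. This stands: a reader might infer that the plan forbids transformation, and the text does not go that far. It does make the wording worth clarifying.

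Second, a condensed article commonly leaves the within-class distribution, distribution checks and selection criterion to a fuller plan, and the named software may fit other distributions. This also stands. Their absence is no fault in itself. The point rests on the input scale that the article does state for its primary outcome.

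Third, the null scenario is artificial. The background section reports associations across domains, and neither skewness, number of scores nor BIC is given. The scenario isolates one mechanism. The percentages show what can happen, and are not the probability of a false profile in this study.

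Fourth, the Phase 2 test would pass any stable artefact, whatever its cause. That is correct. It is a limit of the test and adds no evidence that skewness is present. It shows only that Phase 2 offers no protection.

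Fifth, requiring a profile to persist on a transformed scale can remove real ones, especially a narrow profile such as a purely affective one. The figures above bear this out, so such a rule should not decide alone.

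**Conclusion.** The point holds conditionally. If the within-class model is normal and several scores are clearly right-skewed, a latent profile analysis of raw scores with n = 300 can report profiles where there are none. Under lognormal skew in two or four of 11 scores, the main simulation gave 0–13% of runs at skewness 0.95, 15–75% at 1.32 (one repeat reached 90%) and 77–100% at 1.75. With gamma scores the effect began earlier, at about skewness 1, and was absent at 0.5. Freeing the class variances did not cure it. Normalising the scores did, and the planned Phase 2 comparison would not reveal it.

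A reader might infer that the CEBA profiles will be artefacts. The document does not support that: it gives no score distributions, number of indicators, selection criterion or within-class model, and at low skewness the effect is small or absent. What is supported is a clarification and a comparison fit before the Phase 1 profiles are treated as established.

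**What to change.** In *Primary outcome* and in *Statistical analysis*, 1c:

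1. Say that raw means not norm-adjusted, if that is the intention.
2. Say that for clearly skewed scores the latent profile analysis will also be fitted with a suitable within-class distribution (count, ordinal or skewed) or on a transformed scale (log for time scores). State in advance what counts as clearly skewed, so that the choice does not depend on the profiles obtained.
3. Report both solutions. Label a profile that appears only on the raw scale as possibly a distributional artefact and not as established. Do not delete it automatically.

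The cost is a few lines of text and one more analysis run, with no new data. The downside is that a transformation can hide a genuine small group affected on only one or two scores. Persistence on the transformed scale should therefore inform the decision to retain a profile but not be the sole rule. The wording should be settled before the Phase 1 profile analysis is run.

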#### Neuropsychological tests and questionnaires assessing the CEBA domains

Table 2 lists the CEBA domains and the associated neuropsychological tests that will be used. All tests and questionnaires are commonly used in both research and clinical practice within the Netherlands, and either normative data or data from HCs  are available.

#### Secondary outcomes

Secondary outcomes are the relationships of the CEBA profile with demographic and disease-related characteristics, such as MS subtype, age of disease onset, medication and EDSS (obtained from anamnesis or medical records), and level of societal participation (derived from the score on the Impact on Participation and Autonomy (IPA) questionnaire), all of which are listed in Table 2.

### Data management

The data are stored in an electronic Case Report Form (eCRF) using REDCap [48, 49]. The metadata are stored in the eCRF. Study monitoring will be performed by in-house study monitors from the UMCG. Depending on the type of data and associated privacy regulations, data from the MS-CEBA study will be made publicly available or will become available via the corresponding author upon reasonable request.

### Statistical analysis

For analysing the data, Statistical Package for the Social Sciences (SPSS) version 28.0 and/or R, possibly combined with Latent GOLD version 6.0 [50], depending on the availability of suitable packages in R, will be used. For all analyses, the nominal significance level will be set at α = 0.05, 2 sided. The numbering of the analyses described below corresponds to the numbering of the objectives displayed in Table 1*.* In the following, T0 refers to the first group of 300 PwMS, and T1 refers to the retesting of 54 PwMS.

**Phase 1: Identification of possible CEBA profiles.** 1a) Summary statistics will be computed, describing percentages of PwMS (n = 300) with CEBA symptoms, based on scores on the neuropsychological tests and questionnaires regarding each CEBA domain; 1b) MANOVAs with follow-up ANOVAs will be computed comparing PwMS *(n* = 300) to HCs (*n* = 100) on scores on the neuropsychological tests and questionnaires regarding the Cognitive and Behavioural domain, and ANOVAs will be computed comparing PwMS to HCs on scores on questionnaires regarding the Energetic and Affective domain; for 1c) and 1e) a three-step mixture analysis will be computed [51]: step 1 is a latent profile analysis to identify clusters of PwMS with common CEBA profiles; step 2 is to estimate the posterior cluster membership probabilities of the model from step 1 for each PwMS in the sample, and step 3 is to relate the cluster membership probabilities from step 2 to relevant predictors, i.e., a regression analysis will be carried out to estimate the relationship between the CEBA profiles and the demographic and disease-related variables, with an adaptation to account for the fact that cluster membership is estimated, rather than observed; for 1d) repeated measures MANOVAs will be computed comparing T1 (n = 54) to T0 (n = 300) on the scores on neuropsychological tests and questionnaires for the Cognitive and Behavioural domain separately; if a time effect is indicated, these will be followed by post hoc analyses (repeated measures ANOVAs), to assess which variable(s) the time effect pertains to. A repeated measures ANOVA will be computed comparing T1 to T0 on the scores on questionnaires regarding the Energetic and Affective domain separately; 1f) regression analysis will be carried out, considering two competing models: model 1, using the membership of the CEBA profiles as a predictor; and model 2, using the most distinguishing outcome variables (scores on neuropsychological tests and questionnaires in each of the CEBA domains) as predictors.

**Phase 2: Validation of CEBA profiles and development of the CEBA screening instrument.** 2a) The posterior cluster membership probabilities of the selected latent profile model from Phase 1 will be estimated for each of the PwMS in the new sample (n = 100). The equality of the distributions of membership probabilities of the new sample and Phase 1 sample will be tested using a chi-square test. 

In 2b), development of the screening instrument, and in **Phase 3: Evaluation of the recommended neuropsychological rehabilitation treatment**, no statistical analysis will be performed. 

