## Discussion

To the best of our knowledge, the MS-CEBA study is the first to investigate, over the whole spectrum of CEBA domains, whether there are symptoms in the different domains that consistently occur together in PwMS. In other words, if certain CEBA profiles can be identified, and in turn, how these possible profiles are related to the level of societal participation of PwMS. We believe that increased awareness of and knowledge on the combinations of neuropsychological problems in MS is a meaningful contribution to the literature and to neuropsychological rehabilitation care for PwMS for various reasons.

First, if specific CEBA profiles are indeed discovered, this is an important step in systematically mapping the neuropsychological symptoms that this heterogeneous patient group presents with. This allows for a more structured screening of these combinations of neuropsychological symptoms in PwMS by developing a time-efficient screening instrument taking into account all CEBA domains as well as the highest experienced burden. Standard deployment of the screening instrument in clinical practice, and thereby more consistent and timely attention to the combinations of neuropsychological symptoms of MS, will help prevent these combinations of symptoms from going unnoticed for an extended period of time. Therefore, in the future, PwMS who present with a given CEBA profile will be more timely and fully informed about the most suitable existing neuropsychological rehabilitation treatment options for their profile, and if desired, treatment can be started in a timely manner.

Second, the current dataset will enable the exploration of demographic and medical data as potential predictors for specific CEBA profiles and, additionally, how each corresponding CEBA profile relates to the level of societal participation. This provides insight into potential risk factors for certain CEBA profiles and the corresponding level of societal participation, contributing further to the timely identification of CEBA profiles and, associated with this, the timely indication for neuropsychological rehabilitation treatment in PwMS.

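### With 300 patients against 100 controls, the ordinary ANOVA and MANOVA named for objective 1b do not hold the stated 5% level if the two groups differ in spread; unequal-variance versions correct this at almost no cost

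*Protocol article*

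**What the plan says.** Statistical analysis, Phase 1, item 1b, sets two kinds of patient-control comparison. For the Cognitive and Behavioural domains, "MANOVAs with follow-up ANOVAs will be computed comparing PwMS" with controls. For the other two domains, "ANOVAs will be computed comparing PwMS to HCs on scores on questionnaires regarding the Energetic and Affective domain". The same section states that "the nominal significance level will be set at α = 0.05, 2 sided". The Sample size section gives the group sizes as "our goal of including 300 PwMS and 100 HCs for comparison" and plans 1b "with a medium effect size [Cohen’s f] = 0.5, α = 0.05, power = 0.95", which it says "results in a minimal sample size of n = 60".

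The article does not state a variance assumption, a check of it, or an unequal-variance form of either test. It reports no standard deviations for any score in either group.

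**The concern.** Without a qualifier, ANOVA and MANOVA normally mean the forms that pool the group variances or covariance matrices. Pooling does little harm when groups are of equal size. At 3:1 the pooled estimate is dominated by the 300 patients, while the uncertainty of the mean difference comes mainly from the 100 controls. If patients vary more, the standard error is overstated and the test is too strict. If controls vary more, it is understated and the test is too lenient.

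Objective 1b asks on which domains the groups differ, and the spread ratio may vary from score to score. The real threshold for declaring a difference could then vary from score to score as well, although each test is labelled 5%.

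**Working it through.** **Inputs.** From the article: n₁ = 300 patients, n₂ = 100 controls, two-sided α = 0.05, planning effect f = 0.5 (a standardised difference d = 1.0 for two equal groups). Assumed, because the article gives no SDs: r = patient SD / control SD, shown from 0.67 to 1.6, with control SD set to 1.

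**The plan's own figure.** For f = 0.5, power 0.95 and two-sided α = 0.05, a two-group comparison needs 54 in total at 1:1 and 72 at 3:1. The stated 60 is not reproduced from those inputs; a one-sided 3:1 calculation gives 60. With 400 planned this has no consequence here.

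**Univariate error rate.** The variance of the mean difference that the pooled test uses is, on average,

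V_pooled = [(299r² + 99)/398] × (1/300 + 1/100).

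The true variance is V_true = r²/300 + 1/100. In large samples the pooled test rejects when a standard normal variable exceeds c = 1.960 × √(V_pooled/V_true) in absolute value.

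- r = 1.4: V_pooled = (685.04/398) × 0.013333 = 0.02295; V_true = 0.00653 + 0.01 = 0.01653; c = 1.960 × √1.388 = 2.309; real α = 2.1%.
- r = 0.8: V_pooled = (290.36/398) × 0.013333 = 0.00973; V_true = 0.00213 + 0.01 = 0.01213; c = 1.960 × √0.802 = 1.755; real α = 7.9%.

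| r | c | Real α, pooled |
|---|---|---|
| 0.67 | 1.616 | 10.6% |
| 0.8 | 1.755 | 7.9% |
| 1.0 | 1.960 | 5.0% |
| 1.2 | 2.146 | 3.2% |
| 1.4 | 2.309 | 2.1% |
| 1.6 | 2.450 | 1.4% |

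Simulations agree to about 0.1 point (for example 3.1% at 1.2, 7.8% at 0.8 and 10.5% at 0.67). In the same kind of simulation the Welch test stays at about 5% for every ratio tried from 0.5 to 2. With skewed scores it gives 5.0 to 5.3%.

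**Power when patients vary more.** Take the difference at which Welch has 80% power, so that the expected test statistic is 1.960 + 0.842 = 2.802. The pooled test's power is then Φ(2.802 − c).

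| r | Difference, in root-mean-square SDs | Pooled | Welch | Loss |
|---|---|---|---|---|
| 1.2 | 0.31 | 74.4% | 80% | 5.6 points |
| 1.4 | 0.30 | 68.9% | 80% | 11.1 points |
| 1.6 | 0.29 | 63.7% | 80% | 16.3 points |

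The loss fades as the difference grows. By simulation at r = 1.5, pooled and Welch power are 69% and 82% at d = 0.3, 92.8% and 97.0% at d = 0.4, and 99.3% and 99.8% at d = 0.5. At d = 1.0 both are 100.0% for every ratio tried from 0.67 to 2.

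**Cost of Welch at equal spreads.** At d = 0.3 and r = 1, power is 73.6% pooled and 73.3% Welch, a loss of under 0.4 point.

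**The MANOVA step.** For two groups, MANOVA is Hotelling's test with a pooled covariance matrix. Simulating 300 against 100 with five uncorrelated responses (an assumption; Table 2 lists five cognitive tests) gives a real α of 18.7% at r = 0.67, 1.7% at 1.25 and 0.65% at 1.5.

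**Resampling.** Permuting group labels with the standard MANOVA statistic does not help. Two separate simulations gave a real α of 16.5% and about 20% at r = 0.67, and 0.7% and about 0.5% at r = 1.5. A version built on the unequal-covariance statistic held roughly 5%.

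**The case against.** **The article never says pooled.** It is a condensed account, and a fuller protocol or analysis plan may specify a Welch form or a check of variances. This stands as a limit: the point is a refinement of the tests as named, not a demonstrated error. It does not remove the point, because the article does name a method, and the ordinary meaning of that name is the equal-variance form.

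**The direction is not in the documents.** A reader might infer that patients must be the more variable group, since the Discussion speaks of the symptoms that "this heterogeneous patient group presents with". That sentence concerns the mix of symptoms, not the variance of scores. The Study population section applies the exclusion of other neurological and major psychiatric conditions to patients and controls alike, and controls are matched on age and education. A larger spread in patients is plausible, particularly if distinct profiles exist, since patient scores would then be a mixture. It remains an assumption, which is why ratios on both sides of 1 are shown.

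**The power argument is narrow.** A reader might infer that the study is short of power for 1b. It is not: at the planning effect both tests have power of about 1, and at d = 0.5 the loss is under 1 point. Only differences of roughly 0.4 SD or less are affected.

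**The consequence is small.** The primary outcome is the latent profiles, estimated in patients only. The patient-control comparison is not listed among the secondary outcomes. This stands.

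**Conclusion.** The point holds as a modest improvement. If the ANOVAs and MANOVAs of 1b are run in their ordinary form with 300 and 100 participants, the stated 5% level is correct only when spreads are equal. Over SD ratios from 0.67 to 1.6 the univariate error rate runs from 10.6% down to 1.4%, and the multivariate step departs further. These figures rest on an assumed ratio, on large-sample normal theory confirmed by simulation and, for the MANOVA, on five uncorrelated responses. The univariate figures describe a single ANOVA taken alone, not the full sequence of a MANOVA followed by ANOVAs.

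The documents do not show that power is lost at the effect the study was planned on, that patients are in fact more variable, or that the primary analysis is affected.

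**What to change.** In Statistical analysis, item 1b, name Welch ANOVAs for the univariate patient-control comparisons and, for the Cognitive and Behavioural MANOVAs, a Hotelling-type test that allows unequal covariance matrices. Both changes are needed, because univariate Welch tests leave the MANOVA step as it is. If resampling is preferred for the multivariate step, state that it uses the unequal-covariance statistic.

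The cost is a change of wording and under half a point of power if spreads turn out equal. The multivariate test may have to be run in R, which the plan already names. No change to design, recruitment or data collection follows, and the article reports recruitment as still under way, so the choice can be fixed before analysis.
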